### Outcome Measures

To investigate the efficacy of acupuncture on initial blood pressure fluctuations during laparoscopic hysterectomy, we will compare the difference between the highest and lowest mean blood pressures from the induction of anesthesia to the postincision period as the primary endpoint. As secondary outcomes, systolic, diastolic, and mean blood pressures will be compared at each predetermined timepoint. The incidence of hypotension (systolic blood pressure <90 mmHg or 80% of the baseline), hypertension (systolic blood pressure >160 mmHg or 120% of the baseline), tachycardia, and bradycardia will be recorded. The total use of remifentanil, surgical discontinuation, and length of hospital stay will be assessed as surrogate indicators of stable general anesthesia and surgical procedures.

For patient-reported outcomes, the Spielberger State-Trait Anxiety Inventory (STAI) and EQ-5D-5L will be used to evaluate changes in anxiety and the overall quality of life. The STAI was first validated in 1996 [16,17]. The STAI consists of 40 questions divided into 2 categories: 20 items assessing state anxiety and 20 items assessing trait anxiety. State anxiety refers to experiencing anxiety at the moment, while trait anxiety refers to the type and characteristics of anxiety.

The EQ-5D-5L will be used to assess the effects on the patient’s quality of life. The questionnaire consists of questions in 5 areas: mobility, self-care, usual activities, pain, and anxiety/depression. The EQ-5D-5L assesses the patient’s current state of health. Responses will be provided on a 5-point Likert scale [18].

The study process and timepoints are presented in Figure 1.

**Figure 1 figure1:**
[figure not shown]
Timetable and outcome measurements. NRS: numeric rating scale; STAI: State-Trait Anxiety Inventory. *After the intervention, preoperative, and prior to anesthesia induction.

### Concomitant Care

The participants are not restricted from concomitant care, similar to the conditions in an actual clinical environment. They can choose any type of combination therapy and any necessary salvage treatment throughout the hospitalization period. Researchers will document these therapies in the case report form. Documentation of these therapies will include the type, dosage, route of administration, frequency, and purpose.

### Safety

Safety will be evaluated by grading the severity of the symptoms or medical conditions. Adverse events will be defined according to MedDRA 24.0, and causality will be assessed according to the World Health Organization-Uppsala Monitoring Centre (WHO-UMC) Causality Assessment. The severity of subjective and objective symptoms will be evaluated according to the Common Terminology Criteria of Adverse Events version 5.0.

The clinical study is covered by liability insurance to compensate for any foreseeable or unforeseeable harm that may occur during the research process.

### Sample Size

No prior clinical trial has examined the effect of acupuncture on intraoperative blood pressure fluctuations. As acupuncture is applied as an adjunct to propofol-based general anesthesia in this study, sample size estimation is based on a study comparing mean arterial pressure (MAP) variability between remimazolam and propofol anesthesia [19], which reported MAP fluctuations of 26.7 (SD 9.1) mmHg and 19.5 (SD 7.5) mmHg, respectively. Although the interventions differ, this dataset was considered the best available proxy for estimating between-group differences in MAP variability under general anesthesia.

Using these values, 21 participants per group would be required to achieve 80% power with a 2-sided α of .05 when employing the *t*-test modules, considering that this study is a pilot trial. Assuming a 10% dropout rate due to the short follow-up period, the final sample size has been set at 24 participants per group, totaling 48. All calculations are performed using G*Power version 3.1.9.7 (Heinrich-Heine-University Düsseldorf).

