### Study Process

After a sufficient explanation of the purpose and methods of this clinical study by a researcher, subjects who voluntarily decide to participate and sign a written consent form will be evaluated for eligibility at the screening visit. Eligible subjects will be randomly assigned to the acupuncture or placebo control group according to randomization. Acupuncture treatment will be performed twice, one day before surgery (V1) and on the day of surgery (V2).

All intraoperative management and outcome assessments will be independently performed by anesthesiologists who are not involved in the acupuncture procedure. All participants will fast for 6-8 hours prior to surgery. After entering the operating room (V3), electrocardiography, pulse oximetry, and monitoring of the partial pressure of end-tidal carbon dioxide (IntelliVue MX550; Phillips North America Corporation) will be performed continuously. Automated oscillometric measurements of blood pressure at 2.5-minute intervals and “train of four” (TOF) (ToFscan; Drager Technologies) assessments will also be performed. Throughout the surgery, these data will be downloaded to personal computers using RS232C cables.

After checking the initial vital signs (heart rate, blood pressure, and oxygen saturation) (P1), anesthesia will be induced intravenously with propofol (1-2.5 mg/kg) and remifentanyl (0.01-0.1 ng/kg/min). Mask ventilation (P2) with desflurane will be performed after the administration of rocuronium (0.6-1 mg/kg). Once the TOF ratio reaches <2, the anesthesiologist will perform tracheal intubation (P3). The lungs of the subjects will then be ventilated with desflurane and oxygen in air (FiO2=0.5), and the tidal volume and ventilation rate will be adjusted to maintain the partial pressure of end-tidal carbon dioxide between 35 and 45 mmHg. An additional venous tube will then be secured (P4).

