**Figure 2 figure2:**
[figure not shown]
Flow diagram of the trial.

All participants enrolled thus far are female, reflecting the eligibility condition of requiring total laparoscopic hysterectomy. The mean age of the enrolled participants is 48.3 years. The current dropout rate is 11.4%, and up to the time of this protocol description, all reported adverse events have been mild and unrelated to the intervention.

Final data collection is projected to be completed by December 2025, which will be followed by data cleaning and statistical analysis through March 2026. Publication of the main study results is expected in the latter half of 2026.

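### By the t test that the protocol names, 21 per group give 77.9% power, not 80%; 23 per group are needed, a shortfall of about 2 power points that a wording change repairs at N = 48

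*Protocol article*

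**What the plan says.** All inputs are in the Sample Size section of the protocol article.

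- **Source:** the planning values come from a remimazolam-versus-propofol comparison, "which reported MAP fluctuations of 26.7 (SD 9.1) mmHg and 19.5 (SD 7.5) mmHg, respectively". As worded, remimazolam is the 26.7 mmHg arm and propofol the 19.5 mmHg arm.
- **Requirement:** "21 participants per group would be required to achieve 80% power with a 2-sided α of .05". The calculation is attributed to the t-test module of G*Power 3.1.9.7, and the study is described there as a pilot.
- **Dropout:** 10% is assumed, which raises the number to 24 per group and 48 in total.
- **Caveat given by the authors:** "Although the interventions differ, this dataset was considered the best available proxy for estimating between-group differences in MAP variability under general anesthesia".
- **Background anaesthetic:** "As acupuncture is applied as an adjunct to propofol-based general anesthesia in this study". Study Process confirms that "anesthesia will be induced intravenously with propofol", with desflurane and remifentanil used afterwards.

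The Statistical Analysis section names the Student t test for the primary endpoint. The Results section adds that "The current dropout rate is 11.4" per cent.

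**The concern.** The section gives every input to the calculation: two means, two SDs, the two-sided level, the target power, the test and the software. A reader can therefore repeat it, and the named test does not return the stated number. The sample size and the 80% power claim are what readers will use to judge how informative a non-significant result is, so the figure should agree with its stated method.

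A second matter concerns where the 7.2 mmHg comes from. It is the difference between two anaesthetic drugs, and that drug contrast does not exist between the arms of this trial.

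**Working it through.** **Inputs** (Sample Size section): means 26.7 and 19.5 mmHg; SDs 9.1 and 7.5 mmHg; two-sided α = 0.05; target power 80%; dropout 10%. Allocation is 1:1 (Randomization and Allocation section).

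**Step 1. Effect size.**
- Difference: 26.7 − 19.5 = 7.2 mmHg.
- Pooled SD: √[(9.1² + 7.5²)/2] = √[(82.81 + 56.25)/2] = √69.53 = 8.338 mmHg.
- d = 7.2/8.338 = 0.8635.

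**Step 2. Can 21 be reached?** Three routes come to 21 or close to it.
- Normal approximation, n = 2(1.960 + 0.842)²/d², with d = 0.8635: n = 21.05. This rounds up to 22; power at 21 is 79.9%.
- The same formula with the simple mean SD, (9.1 + 7.5)/2 = 8.3: n = 20.86, which rounds up to 21; power at 21 is 80.3%.
- Two-sided t test with d rounded to 0.9: 21 per group, power 81.2%.

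The documents do not show which route, if any, was taken.

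**Step 3. The named method with the stated inputs.** Under the alternative, the t statistic has 2n − 2 degrees of freedom and noncentrality d√(n/2). At n = 21 the noncentrality is 0.8635 × √10.5 = 2.798, with 40 degrees of freedom and a critical value of 2.021.

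| n per group | Power, pooled SD 8.338 | Power, mean SD 8.3 |
|---|---|---|
| 21 | 77.9% | 78.3% |
| 22 | 79.9% | 80.3% |
| 23 | 81.7% | 82.0% |
| 24 | 83.4% | 83.7% |

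The requirement is 23 per group with the pooled SD and 22 with the mean SD. Using one arm's SD alone gives 27 (SD 9.1) or 19 (SD 7.5). A Welch test at 21 per group also gives 77.9%. A one-sided test with the pooled SD would need only 18. None of these two-sided t-test choices returns 21.

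**Step 4. Dropout.** 21/0.9 = 23.3, rounded up to 24, so the protocol's step is correct for its own starting figure. Starting from 23, 23/0.9 = 25.6, rounded up to 26 per group, or 52 in total.

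**Step 5. What N = 48 delivers for 7.2 mmHg (SD 8.338).**
- No loss, 24 per group: 83.4%.
- 10% loss, 24 × 0.9 = 21.6 per group: 79.1%.
- 21 per group evaluable: 77.9%.

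**Step 6. Smaller differences, 21 per group, SD 8.338.** These differences are assumptions for illustration; the documents support none of them in particular.

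| Assumed difference (mmHg) | Power |
|---|---|
| 6 | 62% |
| 5 | 47% |
| 4 | 33% |
| 3 | 21% |

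**The case against.** The best defence is that the gap is trivial. A normal approximation gives almost exactly 21, and so does a t test with d rounded to 0.9. The trial randomises 24 per group, and power stays between about 78% and 83% under any loss considered here. All of that stands, and it is why the point is minor. It does not make 21 the answer to the calculation as described, because the section names the t-test module and gives unrounded inputs.

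The effect-size side note also meets a fair reply. The authors say that no earlier trial exists, that the interventions differ, and that the data are a proxy. That is open disclosure, and choosing a proxy when direct data are lacking is a matter of judgement.

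Three stronger readings are tempting, and the documents do not support them.

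- *The running dropout leaves only 21 per group for the primary analysis.* The arithmetic is 48 × 0.886 = 42.5, but the article gives neither timing nor reasons for the dropouts. The endpoint is intraoperative while follow-up lasts at least 14 days, so some dropouts may have endpoint data. The primary analysis is also intention-to-treat with multiple imputation.
- *Acupuncture must cut fluctuation by 37%, from 19.5 to 12.3 mmHg.* The quotient 7.2/19.5 = 37% is right, but it takes the cited propofol arm as this trial's control level. Here desflurane and remifentanil follow propofol induction, and the cited study's procedure and measurement window are not given.
- *A plausible effect is 5.3 mmHg, with 60% power.* That comes from applying the between-drug fall (7.2/26.7 = 27%) to 19.5, and it also changes the SD to 7.5. At SD 8.34 the power is only about 51 to 52%, and no part of the article presents 5.3 mmHg as an acupuncture effect.

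**Conclusion.** The stated requirement is wrong by the method that the protocol names: 23 per group, not 21, for 80% power, and 26 rather than 24 per group after the 10% allowance. The shortfall at 21 per group is 2.1 power points. It is a minor error, with no consequence for the conduct of the trial. The result assumes the pooled SD and the exact two-sided t test; with the simple mean SD the requirement is 22, which is still not 21.

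The side note stands in a limited form. The 7.2 mmHg is a contrast between two drugs, and both arms here receive propofol at induction, so it is a planning assumption and says nothing about what acupuncture adds. The documents do not show that it is too large, nor what a better value would be.

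**What to change.** Keep N = 48 and restate the figure in the Sample Size section, for example:

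> 23 evaluable participants per group are required for 80% power. With 24 randomised per group, power for a 7.2 mmHg difference is about 83% with no loss, about 79% with 10% loss, and about 78% if 21 per group are evaluable.

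Add one sentence saying that 7.2 mmHg is a between-drug difference used as an assumption, with power for a few smaller differences at the same SD (for example, about 47% for 5 mmHg at 21 per group). Do not put 5.3 mmHg with SD 7.5 into the protocol as a more plausible effect.

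The cost is a few lines of text and a slightly less favourable power statement. Recruitment, analysis and conduct are unchanged.

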### Statistical Analysis

Both intention-to-treat and per-protocol analyses will be performed, with intention-to-treat being the primary analysis. For per-protocol analysis, the study participants who successfully complete the surgery will be analyzed separately. Successful completion of the surgery is defined as the completion of the scheduled total laparoscopic hysterectomy under general anesthesia without protocol violations, conversion to open surgery, early termination due to intraoperative complications, or major deviations from the anesthetic protocol, such as changes in the anesthetic agents beyond the predefined regimen. For handling missing data, multiple imputations will be performed to obtain estimates and standard errors by setting 10 imputation sets.

The primary endpoint of this clinical trial is the difference between the highest and lowest mean blood pressure measured from anesthesia induction to the postincision period. The Student *t* test will be used to test whether the difference between the 2 groups in the primary endpoint is statistically significant. To account for potential confounding factors affecting the primary outcome, a multivariable linear regression analysis will be conducted. Covariates will include the placebo credibility score (at V1 and V2), anxiety levels (as measured by the STAI and EQ-5D), baseline ward blood pressure (V2), and preoperative blood pressure measured in the holding area prior to operating room entry (V3).

In addition to the primary outcome, secondary outcomes will include hemodynamic stabilization time, incidence of hypotension and hypertension, comparison of drug use, and other efficacy endpoints, including STAI scores. Differences between the 2 groups will be compared using the Student *t* test or Wilcoxon rank sum test, unless otherwise specified. The 2 groups will also be compared by estimating the ratio between the blood pressure measured at each timepoint and that measured at V2, using the blood pressure at V2 as the baseline. Because blood pressure is measured repeatedly, it is not possible to assume independence between measurements; thus, generalized estimating equations will be used. To estimate this ratio, measurements will be log-transformed and included in the model. The 2 groups will be compared using the same method for the pulse rate measured at V2 and the pulse rate at each timepoint. To quantify the length of hospitalization in both groups, we will use Kaplan-Meier estimation to estimate the time until 50% of the participants are discharged. The log-rank test will be used to determine differences in the distribution of discharge times between the 2 groups.

The significance level for all analyses is set at .05. All statistical analyses will be performed using SAS 9.4 (SAS Institute, Inc) or R software 4.1 (R Foundation for Statistical Computing).

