**Methods:**

This is a prospective, single-center, randomized controlled clinical trial with a parallel-group design. Forty-eight adult patients scheduled to undergo a total laparoscopic hysterectomy are eligible for this study. Participants who provide consent will be randomly assigned in a 1:1 ratio to the acupuncture or placebo groups. They will be followed up for at least 14 days to assess the safety of the intervention, general anesthesia, and surgery. Researchers will compare the difference between the highest and lowest mean blood pressures from anesthesia induction to the postincision period as the primary endpoint. As secondary outcomes, systolic, diastolic, and mean blood pressures will be compared at each predetermined timepoint. The incidences of hypotension, hypertension, tachycardia, and bradycardia will be determined separately. The use of remifentanil at the early stage of surgery, rate of surgical discontinuation, and length of hospital stay will be assessed as surrogate indicators of stable general anesthesia and surgical procedures. For patient-reported outcomes, the Spielberger State-Trait Anxiety Inventory and EQ-5D-5L will be used to evaluate changes in anxiety and overall quality of life. This study may support the use of acupuncture as a complementary intervention to help maintain hemodynamic stability during laparoscopic hysterectomy. The study will be conducted in accordance with the Declaration of Helsinki and has been approved by the Institutional Review Board of CHA Ilsan Medical Center (ICHA 2022-11-010; date of approval: January 03, 2023).

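### The supportive per-protocol set can drop patients for events after the primary blood pressure window has closed, and it fixes surgical discontinuation at zero within that set

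*Protocol article*

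**What the plan says.** The Statistical Analysis section plans both intention-to-treat and per-protocol analyses, "with intention-to-treat being the primary analysis". On the second set it states: "For per-protocol analysis, the study participants who successfully complete the surgery will be analyzed separately". It then explains the condition: "Successful completion of the surgery is defined as the completion of the scheduled total laparoscopic hysterectomy under general anesthesia", and this must happen "without protocol violations, conversion to open surgery, early termination due to intraoperative complications, or major deviations from the anesthetic protocol". A change of anesthetic agent outside the planned regimen is given as an example of a major deviation. No criterion is tied to a point in the operation.

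The same section gives the primary endpoint as "the difference between the highest and lowest mean blood pressure measured from anesthesia induction to the postincision period". Outcome Measures frames the aim in the same early-phase terms: "To investigate the efficacy of acupuncture on initial blood pressure fluctuations during laparoscopic hysterectomy".

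The Abstract (Methods) lists among the secondary outcomes: "rate of surgical discontinuation, and length of hospital stay will be assessed". Outcome Measures repeats surgical discontinuation and treats it as a surrogate for stable anesthesia and surgery.

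**The concern.** The rule for entering the per-protocol set looks at the whole operation, while the endpoint looks only at its opening phase. Two of the four exclusions, conversion and early termination, describe how the operation went on or ended. They can occur after the last primary reading and then cannot make that reading invalid.

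They also arise after randomisation. The protocol itself treats discontinuation as an indicator of stability, so it may depend on the treatment or on the same hemodynamic instability that the endpoint measures. Excluding on it selects patients on an outcome, and the retained groups need no longer be comparable. With 24 patients planned per group, a few such exclusions could move the per-protocol contrast.

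The same rule leaves nothing to compare for surgical discontinuation in that set.

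**Working it through.** No figure in the protocol depends on this rule, so there is none to reproduce. The check sets the sections side by side.

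**1. Where the primary window lies.** Study Process labels skin incision P6 and pneumoperitoneum P7. After these come Trendelenburg positioning, ureteral dissection, division of ligaments and vessels, colpotomy, removal of the uterus and closure, and then transfer to postanesthetic care at P8. The window opens at induction and closes in the postincision period. The end of that period is not tied to a numbered timepoint. I assume that it closes soon after P6 or P7, as the early-phase wording suggests.

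**2. When each exclusion can occur.**

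| Exclusion | Possible timing | Can it spoil the primary series? |
|---|---|---|
| Protocol violation | before or during surgery | yes, if before the window closes |
| Conversion to open surgery | only once laparoscopy has begun, so after P6 | not if after the window closes |
| Early termination for complications | any time | only if before the window closes |
| Major anesthetic deviation | any time up to the end | only if before the window closes |

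**3. A test case.** A patient is converted during dissection. All readings from induction to postincision exist and are valid. The scheduled laparoscopic procedure was not completed, so the patient leaves the per-protocol set.

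**4. Surgical discontinuation.** Every member of the set has, by definition, completed the scheduled operation. The count is therefore 0 of n in both groups.

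**5. Size.** Let k1 and k2 be the numbers excluded from two groups of n, and let e be the amount by which the excluded patients' blood pressure range exceeds that of the retained patients, taken as equal in both groups. Dropping k patients lowers a group mean by e × k/n, so the contrast moves by e × (k1 − k2)/n. The protocol gives n = 24 (Sample Size) but not e, k1 or k2. Purely as assumptions, with e = 10 mmHg:

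- k1 = k2: shift 0.
- k1 = 2, k2 = 1: 10 × 1/24 = 0.42 mmHg.
- k1 = 4, k2 = 1: 10 × 3/24 = 1.25 mmHg. The planning difference is 26.7 − 19.5 = 7.2 mmHg, and 1.25/7.2 = 17%.

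If the 10 mmHg is measured against the whole group's mean instead, the last case gives 10 × 4/20 − 10 × 1/23 = 2.00 − 0.43 = 1.57 mmHg, and 1.57/7.2 = 22%. The sign reverses if the other group loses more patients or if e is negative. These lines show how the shift depends on unknown quantities. They do not estimate it.

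**The case against.** The strongest reply is that the per-protocol analysis is only supportive. Every converted or stopped patient stays in the intention-to-treat analysis, where discontinuation and length of stay can be compared in full. This stands, and it limits how serious the point is.

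A second reply is that one set requiring the completed planned procedure is a defensible choice made in advance. Conversion changes the operation, and length of stay runs well past the incision. Protocol violations and departures from the anesthetic regimen are ordinary per-protocol criteria and can fall inside the window. This also stands for whole-operation outcomes. It does not justify removing valid early readings from the primary comparison.

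A third reply is that the section names no per-protocol analysis for any particular secondary outcome, so nobody may intend to compare discontinuation there. That is fair. Still, the general statement that both analyses will be performed exempts no outcome, and one sentence would settle it.

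A reader might infer that the per-protocol analysis ignores whether the needling was received, because the two sessions are not named. The text does not support this. Both sessions are protocol requirements, so a missed one plausibly counts as a protocol violation, and a condensed article may leave the itemised list to the full protocol.

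**Conclusion.** The point holds for the supportive per-protocol analysis only. As worded, the set can lose patients with complete primary data because of a later event that may be related to the outcome, and within it surgical discontinuation is zero by definition. This rests on the postincision period ending early in the operation. A termination before that end could leave the primary series incomplete, and exclusion from the set would then be reasonable.

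The direction and size of any bias are unknown, since no conversion or termination rate is given. Two stronger conclusions may tempt a reader. One is that the per-protocol result cannot serve as a check on the intention-to-treat result. That goes too far: if few patients are excluded for late events, the two sets nearly coincide, and the article reports procedures running without major difficulties. The other is to quote a bias of 17% or 22% of the planned difference. Both figures come from assumed counts and an assumed excess, and the shift is zero in the equal-count case. The point is an inexpensive improvement and not a threat to the main result.

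**What to change.** For the primary endpoint, define the per-protocol set by what happens up to the end of the primary window:

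- no protocol violation before that end, stating that a missed V1 or V2 session counts as one;
- no major anesthetic deviation before that end;
- the primary blood pressure series recorded.

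Do not exclude for conversion, termination or deviation after the window. Tie the end of the postincision period to a stated timepoint so that the rule can be applied. State that surgical discontinuation is compared in the intention-to-treat set only.

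The cost is wording in the protocol or analysis plan, best settled before unblinded analysis. More patients may stay in the set. The one drawback is that the per-protocol set for the primary endpoint may differ from one used for whole-operation outcomes such as length of stay, so each result should state the set it uses.

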### Eligibility

Participants scheduled to undergo surgical removal of the uterus for uterine fibroids and those who have an expected date of total laparoscopic hysterectomy by a gynecologist are eligible. The specific inclusion criteria are as follows: (1) age between 19 and 69 years, (2) American Society of Anesthesiologists (ASA) class I or II, (3) requirement for surgical removal of the uterus by a gynecology specialist, and (4) scheduled to undergo total laparoscopic hysterectomy in advance. All participants will be required to understand and agree with the study protocol. A delegated researcher or research coordinator will obtain written informed consent from all participants.

Participants under the following conditions or situations are ineligible: (1) survival expectancy of less than 3 months; (2) emergency operation, which was not scheduled in advance; (3) hypertension or hypotension that can significantly interfere with the study result; (4) diagnosis of arrhythmia, such as atrial fibrillation and frequent ventricular or supraventricular premature beats; (5) diagnosis of heart failure or valvular disease; (6) anemia with hemoglobin level <12 g/dL; (7) incapable of surgery due to hemodynamic or medical reasons other than stated above; (8) incapable of receiving acupuncture treatment on the determined location; (9) current use of gonadotropin-releasing hormone receptor agonists; (10) current use of drugs that may interfere with the result, including steroids, immunosuppressants, and drugs for psychiatric disorders; (11) significant comorbidities that may interfere with the interpretation of intervention efficacy or results, such as stroke, myocardial infarction, kidney disease, dementia, or epilepsy; (12) pregnant, planning to be pregnant within the study period, or breastfeeding; (13) previous participation in any other clinical trial within 1 month of participation, planning to participate in another clinical trial within 6 months after the enrollment date, or planning to participate in another clinical trial in the follow-up period; (14) failure to complete the informed consent form voluntarily; and (15) being deemed to be unsuitable for participation.

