Another strength of our design is the inclusion of psychological covariates to explore individual variability in response. Although not a primary or secondary endpoint, researchers have incorporated validated tools, such as the Spielberger STAI and EQ-5D-5L, to assess baseline anxiety and quality of life. These tools enable exploratory analysis of whether the psychological state moderates the physiological effects of acupuncture, helping to distinguish autonomically mediated responses from those influenced by psychological factors. This addresses a common limitation of prior acupuncture trials, which often did not account for patient-level psychological differences.

For our primary outcome, researchers chose absolute thresholds of MAP, rather than relative changes, due to inconsistencies in baseline blood pressure definitions in perioperative settings. Establishing a reliable baseline for relative changes is challenging, as preinduction blood pressure often differs from values obtained during preoperative evaluation [38], and normal blood pressure levels can vary depending on individual conditions and circadian rhythms [39]. Given these limitations, researchers have adopted standardized MAP thresholds: values below 65 mmHg are associated with impaired organ perfusion, while sustained elevations above 80 mmHg may increase the risk of major adverse cardiovascular events [40]. These thresholds align with intraoperative blood pressure management goals, providing a clear rationale for selecting them as our primary outcome measure. This standardization, along with the use of 2.5-minute noninvasive blood pressure monitoring, enables close tracking of blood pressure changes during the highly dynamic early intraoperative phase [41].

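### The primary t test and the STAI comparison use no baseline covariate: both are valid but give up precision, with a clear remedy for STAI and a conditional one for the primary endpoint

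*Protocol article*

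**What the plan says.** All references are to the protocol article.

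- **Primary test (Statistical Analysis).** The endpoint is the highest minus the lowest mean pressure between induction and the period after incision. The deciding test is unadjusted: "The Student *t* test will be used to test whether the difference between the 2 groups in the primary endpoint is statistically significant".
- **Additional regression (Statistical Analysis).** "To account for potential confounding factors affecting the primary outcome, a multivariable linear regression analysis will be conducted". Its covariates are listed in two parts: "Covariates will include the placebo credibility score (at V1 and V2), anxiety levels (as measured by the STAI and EQ-5D", and then "baseline ward blood pressure (V2), and preoperative blood pressure measured in the holding area prior to operating room entry (V3".
- **STAI (Statistical Analysis).** STAI scores are listed among the further efficacy endpoints, for which the default is: "Differences between the 2 groups will be compared using the Student *t* test or Wilcoxon rank sum test, unless otherwise specified". Nothing else is specified for STAI.
- **Baseline STAI (Outcome Measures, Discussion).** The instruments are meant to evaluate change. The Discussion says they are used "to assess baseline anxiety and quality of life".
- **Timing of needling (Study Process).** "Acupuncture treatment will be performed twice, one day before surgery (V1) and on the day of surgery (V2".
- **Blood pressure at entry (Eligibility).** One exclusion criterion is "hypertension or hypotension that can significantly interfere with the study result". No section names a pressure reading taken before V1.

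**The concern.** When a pre-treatment value is correlated with the outcome, leaving it out keeps explainable between-patient variation, and the effect of chance imbalance, in the error term. A linear model with that value as covariate estimates the same between-group difference with a smaller standard error. In a trial of this size, a few points of power are worth having if they need no further patients.

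The plan itself lists blood pressure and anxiety as factors that may affect the primary outcome, yet uses them only in a secondary regression. For STAI it reports collecting a baseline on the same scale but names a two-sample test that does not condition on it. At stake is precision. Neither test is biased by the omission.

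**Working it through.** **Inputs from Sample Size and Results.** Mean fluctuations 26.7 (SD 9.1) and 19.5 (SD 7.5) mmHg; two-sided α .05; power 80%; 21 per group, raised to 24 for 10% dropout; current dropout 11.4%.

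**1. The plan's own figure.**
- Difference = 26.7 − 19.5 = 7.2 mmHg.
- Common SD = √((9.1² + 7.5²)/2) = 8.34; standardised difference = 7.2/8.338 = 0.863.
- The normal approximation gives 22 per group and the exact t calculation 23, close to the stated 21. Power at 21 per group is 79.9% (normal) or 77.9% (exact t). The exact t figure is the reference below.
- Dropout: 21/0.9 = 23.3, so 24 per group, as stated.
- Evaluable patients: 2 × 21 = 42, or 48 × (1 − 0.114) = 42.5 at the current dropout rate.

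**2. Primary endpoint with one pre-treatment covariate.** Let ρ be the within-group correlation of the covariate with the pressure range. The protocol gives no value, so ρ is assumed. The residual variance is multiplied by (1 − ρ²), chance covariate imbalance inflates it by 1 + 1/(42 − 4) = 1.026, and the degrees of freedom fall from 40 to 39. The effective standardised difference is 0.863/√((1 − ρ²) × 1.026).

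| Assumed ρ | Relative variance | Power, 21 per group |
|---|---|---|
| t test, no covariate | 1.000 | 77.9% |
| 0 | 1.026 | 76.8% |
| 0.2 | 0.985 | 78.5% |
| 0.3 | 0.934 | 80.6% |
| 0.4 | 0.862 | 83.6% |
| 0.5 | 0.770 | 87.5% |

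The covariate breaks even at ρ of about 0.16. The change is −1.1 points at ρ = 0, +2.7 at 0.3 and +9.6 at 0.5.

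**3. STAI.** With equal SD σ before and after treatment, the per-patient variances in large samples are:
- post-score test: σ²
- change-score test: 2σ²(1 − ρ)
- ANCOVA: σ²(1 − ρ²)

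So ANCOVA has (1 − ρ²) times the post-score variance and (1 − ρ²)/(2(1 − ρ)) = (1 + ρ)/2 times the change-score variance.

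| Assumed ρ | Versus post-score | Versus change score |
|---|---|---|
| 0.3 | 0.91 | 0.65 |
| 0.5 | 0.75 | 0.75 |
| 0.7 | 0.51 | 0.85 |

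Neither ratio exceeds 1, so in large samples ANCOVA is no worse than either simple test. In this sample it costs one degree of freedom and the 1.026 factor.

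**4. Which pressures can serve.** The first needling is at V1. The ward pressure is from V2 and the holding-area pressure from V3, so both follow at least one session. The credibility scores belong to the needling visits themselves. Treatment may have moved any of these, and adjusting for them could remove or distort part of the effect under study.

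**The case against.** The case on the other side is substantial.

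- **The t test is valid and matches the sample-size method.** This stands. A reader might infer that the unadjusted test is an error. It is not; the point is one of efficiency.
- **An adjusted analysis is already planned.** It is, but it is not the deciding test, so it adds nothing to that test's power. It also includes variables measured after needling began. Counting about seven covariates, it would have to explain about 19% of the outcome variance to break even on power, against about 3% (0.16²) for a single covariate.
- **No pre-needling blood pressure is documented.** This stands. A reader might infer from the exclusion criterion and from admission the day before surgery that such a reading is available. That makes one likely, but the article does not state it. The timetable figure is not shown, and device and timing are unknown.
- **The gain on the primary endpoint is assumed.** This stands. The range has no baseline counterpart. It depends on responses to intubation and incision and on titrated drugs as well as on resting pressure, and the entry criteria narrow the spread of resting pressure. A gain of about 10 points needs ρ = 0.5, which nothing in the article supports.
- **The STAI sentence is a default in a condensed article.** It could cover a t test on change scores, which does use the baseline. That is why both comparisons are shown; at ρ = 0.7 the cut against a change score is 15%. The Discussion also says these tools are neither primary nor secondary endpoints, which limits the weight of this part.

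**Conclusion.** The concern holds as a point about precision. The deciding test of the primary endpoint and the named tests for STAI use no baseline covariate, in about 42 evaluable patients.

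For STAI the improvement is concrete and nearly free, because the baseline is reported as collected. Its size depends on the correlation: at ρ = 0.5 the large-sample variance is 25% lower than with either simple test. It assumes that the baseline score precedes the V1 session, which must be confirmed.

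For the primary endpoint the improvement is conditional on a pressure recorded before V1 and on a correlation above about 0.16. Power could move from 77.9% to anywhere between 76.8% and 87.5% for ρ from 0 to 0.5, and the gain may be small. It would go too far to say that the trial forgoes a known gain at no cost: for this endpoint the covariate is undocumented, the correlation is unknown, and a useless covariate costs about 1 point of power.

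**What to change.** 1. **STAI (main change).** In Statistical Analysis, replace the t or Wilcoxon comparison with ANCOVA of the post-intervention score on group and the baseline score of the same scale (state with state, trait with trait). Confirm first that the baseline is taken before V1 needling. Cost: one degree of freedom and a change of wording.
2. **Primary endpoint (only if the data exist).** Check whether a mean blood pressure was recorded at screening or admission, before the first needling. If so, make the primary test a linear model of the pressure range on group plus that single covariate. Report the adjusted difference with its 95% confidence interval and keep the Student t test as a sensitivity analysis. Cost: one degree of freedom, about 1 point of power if the covariate is unrelated to the outcome, and possibly transcription into the case report form. If no such reading exists, leave the t test as the primary test.
3. **Covariates to avoid here.** Do not use the V2 or V3 pressures or the credibility scores as this covariate.

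Fix these choices in writing before unblinding. No additional patients or visits are needed.
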